## Abstract

**Background:**

The International Network for Evaluating Outcomes in Neonates (iNeo) is a collaboration of population-based national neonatal networks including Australia and New Zealand, Canada, Israel, Japan, Spain, Sweden, Switzerland, and the UK. The aim of iNeo is to provide a platform for comparative evaluation of outcomes of very preterm and very low birth weight neonates at the national, site, and individual level to generate evidence for improvement of outcomes in these infants.

**Methods/design:**

Individual-level data from each iNeo network will be used for comparative analysis of neonatal outcomes between networks. Variations in outcomes will be identified and disseminated to generate hypotheses regarding factors impacting outcome variation. Detailed information on physical and environmental factors, human and resource factors, and processes of care will be collected from network sites, and tested for association with neonatal outcomes. Subsequently, changes in identified practices that may influence the variations in outcomes will be implemented and evaluated using quality improvement methods.

**Discussion:**

The evidence obtained using the iNeo platform will enable clinical teams from member networks to identify, implement, and evaluate practice and service provision changes aimed at improving the care and outcomes of very low birth weight and very preterm infants within their respective countries. The knowledge generated will be available worldwide with a likely global impact.

## Background

The global incidence of preterm birth is on the rise [1]. In Canada the incidence of preterm birth (<37 weeks gestational age) has increased from 6.3% in 1981 to 7.7% in 2009 [2,3]. Although infants born at a very low birth weight (VLBW, <1500 g) and/or very preterm (VPT, <32 weeks gestational age) make up only 14% of all preterm births in Canada [3], they are of significant public health importance due to their high risk of mortality and childhood morbidities. These morbidities include developmental problems, cerebral palsy, cognitive delay, blindness, and deafness [4,5], with an estimated lifetime cost of CAD$676,800 per preterm infant with permanent disability [6]. Therefore, it is important to identify strategies that will reduce the risk of adverse outcomes suffered by VLBW and VPT infants and improve quality of life for these infants.

Various national neonatal networks, such as the Australia-New Zealand Neonatal Network (ANZNN) [7], Canadian Neonatal Network (CNN) [8], Israeli Neonatal Network (INN) [9], Neonatal Research Network of Japan (NRNJ) [10], Swedish Neonatal Quality Register (SNQ) [11], and UK Neonatal Collaborative (UKNC) [12], have been established to collect data from their constituents and identify trends in the outcomes of VLBW infants and benchmark the performance of their respective centers. Although advances in neonatal care between the 1960s and the 1990s resulted in significant reductions in mortality and morbidity for neonates [13-16], recently some networks, including the CNN, have observed a halt in progress or even worsening of outcomes [13,17-19].

Even for those neonatal networks where continued improvements in outcomes have been reported, there remains significant variation within and between networks. For example, several comparative studies have identified differences in mortality rates in neonates from separate networks, regions, or countries [20-27]. In one such study, Draper et al. reported that among 10 European regions, the overall survival rate for VPT infants varied from 74.8% to 93.2% [21]. More recently, in 2012 population data from the UKNC showed a greater than three-fold variation between regional networks in the percentage (range 4.7% to 16.6%) of infants born at <30 weeks gestation and admitted to neonatal units who died at ≤28 days of age [27]. Comparison of selected Australian and Scottish neonatal intensive care units (NICUs) detected a lower risk-adjusted mortality rate for VPT/VLBW infants in Australia compared with Scotland [28].

However, studies of a single or small group of sites are subject to selection bias, which can lead to erroneous conclusions when the results are generalized to the larger population. Furthermore, comparisons of mortality alone may be misleading as mortality may be declining at the cost of increasing morbidities. Measurement of mortality as an indicator of care is also a contentious issue as there are marked variations in practice between countries including initiation or withholding of resuscitation at earlier gestational ages [29]. Thus, this protocol for the International Network for Evaluating Outcomes of Neonates (iNeo) was developed to examine neonatal morbidities in conjunction with mortality using population-based data, and assess variations in practice that impact outcomes between and within countries.

### Rationale

Over the past 5 years, collaborations have been initiated between the CNN, NRNJ, ANZNN, and SNQ. The first ever population-based retrospective comparison between countries showed that a composite outcome of mortality or any major morbidity (bronchopulmonary dysplasia [BPD], severe neurological injury, ≥stage 3 retinopathy of prematurity [ROP], nosocomial infection [NI], and ≥ stage 2 necrotizing enterocolitis [NEC]) was lower in VLBW infants in Japan compared with Canada. In-depth analyses revealed higher rates of severe neurological injury, NEC, and NI among NICUs in the CNN, whereas rates of BPD and ROP were higher in NRNJ NICUs [30]. Comparisons between the CNN and the ANZNN for VPT infants identified that while there was no difference in mortality, the ANZNN had significantly lower rates of severe neurological injuries, ROP, NEC, and BPD, but higher rates of early onset sepsis and air leaks and longer mean length of stay [31,32]. Our latest comparisons indicated that rates of adverse outcomes at each gestational age were lower in Sweden compared with Canada (unpublished data).

Differences in the outcomes of VLBW and VPT infants between Canada and other countries could be due to any number of factors including differences in population characteristics, severity of illness, processes of care, or delivery of health care. Informal discussion has confirmed wide variations in these factors between networks. For example, compared with Canada, the use of non-invasive respiratory support is higher in Europe, the use of breast milk is higher in Japan and Scandinavia, and the use of echocardiography by neonatologists for hemodynamic monitoring is routine in Japan. Differences in the type of intervention and process of administration may underlie at least some of the variations in outcomes. In addition, there are extreme variations in health services delivery and receipt. For example, the number of outborn, very preterm infants is significantly lower in the ANZNN compared with the CNN [32]; the use of respiratory therapists is practically non-existent in European countries, whereas they play a prominent role in North American institutions; and shift work is more prevalent among junior doctors in Europe and Australia [33] compared with Canada.

Given the variation in mortality and morbidity between countries, it is important to first characterize factors underlying these differences, and then identify areas and approaches to improve neonatal care specific to each network. Care provision to VLBW and VPT infants is a highly selective health service where specialized units deliver the majority of such care (approximately 80% of VLBW and VPT infants are admitted to tertiary NICUs), and consumes extensive resources, both in terms of the per-diem cost of caring for such a neonate in the NICU and cumulative lifetime costs. To improve outcomes and reduce health care costs globally, we need to embrace the concept of collaborative sharing and learning, assess the variation in practices between countries/networks, identify evidence-based practices associated with improved outcomes, and apply these practices to deliver optimal health care to fragile neonates.

Currently, informal and indirect comparisons can be made from the reports published by each national network. However, criticisms of such indirect or post-hoc comparisons include lack of adjustment for differences in baseline infant and maternal characteristics, differences in definitions of outcomes and their measurement, and variations in physical, environmental, and human factors (e.g. training system and associated working conditions of physicians on duty day and night, differences in nursing care and nurse:beds ratio, differences in regionalization system, and the rate of maternal transfer for extremely preterm fetuses). A system of data standardization and an understanding of the context for comparison are urgently needed to enable valid comparisons between networks. This can only be achieved through an international collaboration where the knowledge users and decision makers are involved from the start of the process and continuously through to knowledge translation. Analyses of network-level data using all eligible infants will provide a more accurate estimate of the effectiveness of an intervention in a pragmatic setting, rather than just a measure of efficacy proven in a controlled study setting.

### Network objectives

The specific aims of iNeo are to:

– 1. Compare outcomes for infants born with VLBW (weighing <1500 g) and VPT (<32 weeks gestation) among eight national neonatal networks spanning nine countries.

– 2. Identify site-level physical, human, and environmental characteristics, as well as care practices that are associated with variations in outcomes.

– 3. Identify clinical and organizational practice improvements relevant to each network.

– 4. Implement and continually evaluate the impact of evidence-based clinical and organizational practice changes in NICUs within the iNeo networks.

The establishment of the iNeo collaboration will enable the following: i) collection and integration of individual-level data from population-based networks on outcomes, characteristics, practices, and culture of the member sites; ii) evaluation of the impact of practice and outcome variations to identify the best models of health service delivery (incorporating medical and other extraneous factors); iii) feedback to units of their standing in reference to each and all other networks; iv) empowerment of units to embrace implementation of evidence-based practice changes for quality improvement; and v) performance of ongoing cycles of translating knowledge-to-action through continuous auditing. Ultimately, this will improve outcomes for VLBW infants across the iNeo member networks.

## Methods/design

### Overview

The comparison of neonatal mortality and morbidity between the eight member networks will be conducted using four years of retrospective data collected between January, 2007 and December, 2010. Subsequently, a strategy will be designed to collect additional data and assess differences in physical, environmental, and human characteristics, and care practices associated with variations in outcomes between networks. Once identified, clinical and organizational practice improvements will be implemented within networks using the Evidence-based Practice for Quality Improvement (EPIQ) method [34,35]. The effect of practice change implementation will be measured using ongoing data collection within each network. The total study period will be five years (January 2013 to December 2017). Comparison between the networks will be completed by early 2014, associations between external factors/care practices and outcomes identified by the end of 2014, and selected practice changes implemented by mid 2015. This will be followed by a two and a half-year period of continuous quality improvement within the networks.

### Participating networks

The following neonatal networks have agreed to participate in the iNeo project: Australia-New Zealand Neonatal Network (ANZNN), Canadian Neonatal Network (CNN), Israeli Neonatal Network (INN), Neonatal Research Network of Japan (NRNJ), Spanish Neonatal Network (SEN1500), Swedish Neonatal Quality Register (SNQ), Swiss Neonatal Network (SNN), and UK Neonatal Collaborative (UKNC) (see Table 1). Overall, this project will be collecting data from a total of 251 NICUs in nine countries caring for approximately 23,000 to 24,000 VLBW neonates per year. All the participating networks have a common mandate to collect, analyze, and benchmark performance and outcomes of their respective NICUs. We have carefully avoided networks that only include highly specialized units in order to obtain robust population-based estimates. All participating networks have confirmed the feasibility of data collection from >75% of all VLBW and VPT infants born within their country. The approximately 25% of infants missing from some of the networks are those considered to be at the higher end of maturity (>1300 g birth weight or >30 weeks gestation) who do not require intensive care support. These infants are relatively stable and do not represent a significant burden to NICUs or health care services in general.

**Table 1 T1:** Characteristics of networks participating in the International Network for Evaluating Outcomes of Neonates (iNeo)

**Network**	**Australia and New Zealand Neonatal Network**	**Canadian Neonatal Network**	**Israeli Neonatal Network**	**Neonatal Research Network Japan**	**Spanish Neonatal Network**	**Swedish Neonatal Quality Register**	**Swiss Neonatal Network & Follow-****Up Group**	**UK Neonatal Collaborative**
Country	Australia and New Zealand	Canada	Israel	Japan	Spain	Sweden	Switzerland	UK (England)
Level III NICUs in the country	23 + 6	30	23	93	n/a	7	9	45
Level III NICUs in the network	29	30	23	73	36	7	9	44
Number of inhabitants	Australia: 23 million NZ: 4.4 million	34 million	7.9 million	126 million	47 million	9.5 million	8 million	52 million
Number of births/year	Australia: 300,000 NZ: 60,000	380,863	166,000	1,071,304	497,023	110,000	80,000	687,000
Number of eligible NICU admissions/year (<32 wks gestation/<1500 g)	3,500	2,700	1,500	3,700	2,600	900	800	7,700

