### Comparisons of neonatal outcomes between networks

#### Outcomes

The primary outcome for comparison between the networks will be a composite indicator of mortality or any of the four major neonatal morbidities (severe neurological injury, severe ROP, NEC, and BPD). Mortality will be defined as death due to any cause prior to discharge home. Severe neurological injury will be defined as ≥ stage 3 intraventricular hemorrhage (IVH) with ventricular dilatation according to the criteria of Papile et al. [38], or parenchymal injury (including periventricular leukomalacia) with or without IVH. Severe ROP will be defined as ≥ stage 3 according to the International Classification [39], or need for laser surgery or intraocular injections of anti-vascular endothelial growth factor agents. NEC will be defined as ≥ stage 2 according to Bell’s criteria [40] and BPD as oxygen requirement at 36 weeks post-menstrual age [41].

Secondary outcomes to be compared among iNeo member networks will include the individual morbidities of the composite outcome, as well as nosocomial infection defined as culture-proven sepsis (blood or cerebrospinal fluid positive for pathogenic organism) at >3 days or 72 hours postnatal age [42], patent ductus arteriosus requiring pharmacological treatment and/or surgical ligation, receipt of delivery room cardiopulmonary resuscitation, air leak syndrome, and resource utilization (length of stay and length of respiratory support). To account for potential differences in practices regarding discharge home and transfer to Level 2 community units, additional analyses will compare mortality by Day 28 after birth. All outcomes will be expressed as ratios with the denominator equal to all admissions to participating NICUs.

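### The claim that every network can capture more than 75% of VLBW/VPT births does not fit the article's own Canadian figures, and low-risk infants are missing from only some networks, which can bias the full-cohort comparison

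*Protocol article*

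**What the plan says.** Under Participating networks the protocol article states that "All participating networks have confirmed the feasibility of data collection from >75% of all VLBW and VPT infants born within their country". It continues: "The approximately 25% of infants missing from some of the networks are those considered to be at the higher end of maturity", gives the range as above 1300 g or above 30 weeks, and explains that these infants do not need intensive care.

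The Background gives the Canadian incidence. Preterm birth "has increased from 6.3% in 1981 to 7.7% in 2009", and VLBW and/or VPT infants "make up only 14% of all preterm births in Canada". Table 1 lists births and eligible NICU admissions per year for each network.

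Under Outcomes, "All outcomes will be expressed as ratios with the denominator equal to all admissions to participating NICUs". This covers the primary composite of mortality or any of four major morbidities. The Background also notes that countries differ markedly in "initiation or withholding of resuscitation at earlier gestational ages". The planned adjustment uses predictors such as gestational age, sex, plurality and antenatal steroids, plus a severity-of-illness score scaled from 0 to 1 within each network.

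**The concern.** Two statements bear on whether the networks are comparable. The first is a coverage claim made for all networks, which can be checked against the article's own numbers for at least one of them. The second is the description of who is missing: infants with a good prognosis, and only in some networks. A network that does not record its low-risk infants has a smaller denominator with almost the same number of events, so its rate rises without any difference in care.

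The between-network comparison drives the rest of the programme. It produces the funnel plots, identifies well-performing networks and those with room to improve, and points to the practices to be changed. A network flagged because of whom it admits would send that effort in the wrong direction.

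**Working it through.** **Totals.** The Table 1 figures reproduce the stated totals: 251 Level III units, 23,400 admissions a year, 4 × 2,700 = 10,800 for Canada and 4 × 20,700 = 82,800 for the other networks. The table is therefore the basis of the plan's own calculations.

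**Coverage in Canada, the only country where the article gives every input.**
- Inputs: 380,863 births a year and 2,700 eligible admissions (Table 1); 7.7% preterm and a 14% VLBW/VPT share (Background).
- Expected infants: 380,863 × 0.077 × 0.14 = 4,106.
- Coverage: 2,700 / 4,106 = 65.8%.
- Lowest value at the rounding limits: 2,650 / (380,863 × 0.0775 × 0.145) = 2,650 / 4,280 = 61.9%.
- Highest value at the rounding limits: 2,750 / (380,863 × 0.0765 × 0.135) = 2,750 / 3,933 = 69.9%.
- Coverage of 75% would need 0.75 × 4,106 = 3,079 admissions. Alternatively, the denominator would have to be 2,700 / 0.75 = 3,600, which is 506 infants (12%) fewer.

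**Other networks, supportive only.** Eligible admissions per 100 births:

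| Network | Admissions / births | Per 100 births |
|---|---|---|
| Japan | 3,700 / 1,071,304 | 0.35 |
| Spain | 2,600 / 497,023 | 0.52 |
| Canada | 2,700 / 380,863 | 0.71 |
| Sweden | 900 / 110,000 | 0.82 |
| Israel | 1,500 / 166,000 | 0.90 |
| Australia/New Zealand | 3,500 / 360,000 | 0.97 |
| Switzerland | 800 / 80,000 | 1.00 |
| UK (England) | 7,700 / 687,000 | 1.12 |

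For 75% coverage, the VLBW/VPT incidence could be at most 0.345 / 0.75 = 0.46% in Japan and 0.523 / 0.75 = 0.70% in Spain. Japan also has 93 − 73 = 20 Level III units outside the network. Intensive care units are unlikely to be missing only stable, mature infants. The article gives no incidence for either country, so no coverage figure follows.

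**Effect of omitting low-risk infants, crude and on assumed rates.** If a share m of the cohort with event rate q is not recorded and the full-cohort rate is r, the recorded rate is (r − m·q) / (1 − m). With q = 10% (assumed):

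| Full-cohort rate r (assumed) | m = 10% | m = 25% |
|---|---|---|
| 30% | 32.2% (+2.2 points) | 36.7% (+6.7) |
| 40% | 43.3% (+3.3 points) | 50.0% (+10.0) |

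The power section claims detectable differences of 0.4 to 3 points. The shifts in this table are before adjustment and show direction and order of size only.

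**What the adjustment can do.** The omitted infants lie mainly at higher gestational ages, so adjusting for gestational age removes part of the shift. It cannot remove selection on need for intensive care among infants of the same gestational age. A severity score bears on that selection, but only most networks collect one, and scaling it within each network weakens it as a measure of differences between networks. The Day 28 mortality analysis addresses discharge and transfer practice, not admission.

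**The case against.** The quoted sentence speaks of feasibility, not achieved coverage. The Canadian denominator combines a 2009 preterm rate with a birth count of unstated year, and it may include stillbirths or delivery-room deaths that can never become admissions. These points stand as caveats and soften the 66%. They do not reconcile the figures. If deaths before admission are the explanation, the cohort falls short of infants born for that reason.

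A reader might infer that Japan demonstrably fails as well, for example by multiplying 73/93 units by the general statement that "approximately 80% of VLBW and VPT infants are admitted to tertiary NICUs", which gives 63%. The article does not support this. The 80% is not attributed to Japan, equal unit size is assumed, and the same method gives Canada 30/30 × 80% = 80%, at odds with the 66% above. Nor can Canada's incidence of 1.08% (0.077 × 0.14) be carried across: applied to the UK it gives 1.121 / 1.078 = 104% coverage.

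A reader might also set the crude shifts directly against the detectable differences and conclude that selection swamps the primary comparison. The planned inference is adjusted, the rates are assumed, and nothing in the article gives the residual bias. Likewise, the article acknowledges differing resuscitation practice and gives it as a reason to study morbidity alongside mortality. Selection at the immature end is plausible, but its size cannot be computed.

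Finally, restricted analysis sets are often left to a fuller document. That is fair for the detail. It does not cover a coverage statement that the article's own numbers do not support.

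**Conclusion.** The blanket claim of more than 75% is not supported. Canada comes to about 66% (62% to 70% at the rounding limits), assuming that the birth count and the incidence describe similar years and populations. One such case is enough against a statement about all networks. Japan and Spain look low, but this is supporting evidence only.

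Differential selection on prognosis is stated in the article itself. Combined with the admissions denominator, it can bias the full-cohort comparison of the primary composite against networks that omit low-risk infants. The planned adjustment should reduce this bias but not remove it, and the remaining size is unknown.

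It would go too far to say that the primary population must be replaced. Narrowing it would give up primary inference on the more mature infants, and that trade-off is debatable. The article also never says that capture is complete at or below 30 weeks and 1300 g, only that the known gaps lie above those limits.

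**What to change.** 1. Replace the general statement with estimated coverage for each network, giving numerator, denominator and year wherever national VLBW/VPT birth counts exist. State where they do not.
2. Describe the cohort as based on NICU admissions.
3. Pre-specify a key sensitivity analysis of the primary between-network comparison, restricted to infants of at most 30 weeks and at most 1300 g. This excludes the range that the article names as incompletely captured. Set any lower gestational limit from the networks' own admission data, before outcomes are compared.
4. Call a network an outlier on the primary composite only if the finding is consistent in the restricted set. Keep the full cohort as the primary population.

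Cost: gestational age and birth weight are already in the minimum dataset, so the restricted analysis needs no new infant-level data. Coverage per network does need national birth counts from outside the admissions dataset. The restricted analysis has fewer infants and less precision, and it does not recover infants treated in non-member units.
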